#### Sample size calculation

2.2.4

The sample size calculation was conducted using G*Power 3.1.9.7, selecting the F-test family and the “ANOVA: Repeated measures, within-between interaction” option. The calculation targeted the omnibus longitudinal group-by-time interaction in a design with three groups and three assessment points. The effect size was entered as Cohen’s *f* = 0.16, which represents a small effect and is approximately comparable to a standardized effect of *d/g* ≈ 0.32 under a simple two-group contrast approximation, based on prior meta-analytic findings that report small but consistent effects of app-based interventions on psychological well-being among university students (26). To account for the two co-primary outcomes, the alpha level was adjusted to α = .025 using a Bonferroni correction. The remaining parameters were statistical power = .95, correlation among repeated measures = .50, and nonsphericity correction *ϵ* = 1. Under these assumptions, the required analytical sample size was 141 participants, corresponding to 47 participants per group, with an actual power of .9509. To allow for an anticipated attrition rate of approximately 20%, the recruitment target was increased to 177 participants, corresponding to 59 participants per group.

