##### Primary outcome measure: psychological well-being

2.2.7.3

The primary outcome of the study will be psychological well-being, operationalized through two co-primary measures: global positive mental well-being assessed with the Warwick–Edinburgh Mental Well-Being Scale (WEMWBS (53)) and emotional, psychological and social well-being assessed with the Mental Health Continuum–Short Form (MHC-SF (54)).

The WEMWBS (53) is a 14-item self-report scale designed to measure positive mental well-being as a central component of optimal psychological functioning. Each item is rated on a 5-point Likert scale, ranging from 1 (“none of the time”) to 5 (“all of the time”), producing a total score from 14 to 70, with higher scores reflecting greater well-being. The WEMWBS has demonstrated excellent internal consistency, with Cronbach’s α typically exceeding .88 across samples, and strong test–retest reliability. Validation studies in Spanish university populations confirm its robust psychometric performance, with α values above .85 and expected associations with related constructs of well-being and mental distress.

The MHC-SF (54) is a widely used instrument for assessing emotional, psychological, and social well-being. It consists of 14 items covering positive affect, personal functioning, and social connectedness, each rated on a 6-point scale, ranging from 0 (“never”) to 5 (“every day”). For the present study, the continuous scoring method will be applied, producing scores ranging from 0 to 70, with higher scores indicating greater positive mental health. The MHC-SF has shown excellent reliability, with internal consistency ranging from α = .80 to .89 in community and student populations. Evidence from Spanish validation studies demonstrates high internal consistency (α = .83–.89), strong construct validity, and sensitivity to changes in well-being among university students.

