To control the family-wise Type I error rate across the two co-primary outcomes, a Bonferroni-adjusted significance threshold of α = .025 will be applied to the primary confirmatory group-by-time interaction test for each outcome. *Post hoc* pairwise comparisons among the three groups (PPIA vs. WLCG, PPIA+M vs. WLCG, and PPIA+M vs. PPIA) will be conducted using estimated marginal means at post-intervention (T2) and six-month follow-up (T3). Pairwise contrasts will be adjusted using the Bonferroni correction. Effect sizes will be calculated using Cohen’s *d* and interpreted as small (*d* < 0.50), moderate (*d* = 0.50–0.79), or large (*d* ≥ 0.80), following the guidelines proposed by Cohen (63).

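### The fixed Bonferroni split across WEMWBS and MHC-SF is valid, but Holm's procedure gives the same 5% family-wise error with slightly more power at no cost in sample size (low priority)

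*Protocol article*

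**What the plan says.** Section 2.2.7.3 defines one primary construct measured by two scales: "The primary outcome of the study will be psychological well-being, operationalized through two co-primary measures". These are WEMWBS and MHC-SF.

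Section 2.2.4 sizes the trial on the "omnibus longitudinal group-by-time interaction in a design with three groups and three assessment points", with f = 0.16, power .95, correlation among repeated measures .50 and no nonsphericity correction. On alpha it states: "To account for the two co-primary outcomes, the alpha level was adjusted to α = .025 using a Bonferroni correction". The result is 141 analysed (47 per group) with actual power .9509, raised to 177 (59 per group) for about 20% attrition.

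Section 2.2.9 fits a separate mixed model to each scale and fixes the confirmatory rule: "To control the family-wise Type I error rate across the two co-primary outcomes, a Bonferroni-adjusted significance threshold of α = .025 will be applied" to the interaction test of each scale. It mentions no step-down procedure.

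**The concern.** Testing each scale at its own .025 implies that either scale can succeed alone. For that kind of claim a fixed Bonferroni split spends more than it needs to. Once one scale has passed at .025, the other can be tested at the full .05 without raising the family-wise error. Under the plan as written, if one scale is clearly significant and the other has p = .03, the second must be declared not significant. Under Holm it would be confirmed.

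What is at stake is some power to confirm the second scale. A smaller matter goes with it: the hypotheses are worded for psychological well-being as a whole, and the article does not say how a result on one scale only would be worded.

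**Working it through.** **1. Inputs.** From section 2.2.4: f = 0.16, N = 141 (47 per group), 3 groups, m = 3 assessments, ρ = .50, ε = 1, α = .025 per scale. The correlation r between WEMWBS and MHC-SF is not given and is assumed, over the range 0 to .9.

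**2. Reproducing the plan's figure.**
- λ = f² × N × m / (1 − ρ) = 0.0256 × 141 × 3 / 0.5 = 21.66.
- Degrees of freedom are (3 − 1)(3 − 1) = 4 and 2 × (141 − 3) = 276.
- The noncentral F distribution gives power .9510 at α = .025 (stated: .9509) and .9735 at α = .05.
- Recruitment is 141 / 0.8 = 176.25, or 177 when rounded up to equal groups.

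The stated alpha, sample size and power agree with each other.

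**3. Error control under Holm.**
- If both nulls are true, an error needs the smaller p-value to be at most .025. The probability is at most .025 + .025 = .05, the same as under Bonferroni.
- If one null is true, an error needs that scale's p-value to be at most .05, so the probability is at most .05.
- Neither step uses the correlation.
- Simulation (400,000 runs per setting) agrees. Under the global null the error is .049 at r = 0 and .037 at r = .9 for both procedures. With one true null, Holm rejects it in .048 to .049 of runs.

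**4. Power to confirm both scales, independent case (exact).**
- Bonferroni: .9510² = .904.
- Holm confirms both when both p-values are at most .05 and they do not both lie between .025 and .05: .9735² − (.9735 − .9510)² = .9477 − .0005 = .947.

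**5. Power with correlated scales, f = 0.16 on both, N = 141 (simulation).**

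| r (assumed) | Both, Bonferroni | Both, Holm | Gain (points) | At least one, either procedure | Split, Bonferroni | Split, Holm |
|---|---|---|---|---|---|---|
| .5 | .913 | .950 | 3.7 | .989 | .076 | .040 |
| .7 | .920 | .953 | 3.3 | .982 | .062 | .030 |
| .8 | .924 | .954 | 3.0 | .977 | .052 | .022 |
| .9 | .932 | .957 | 2.5 | .970 | .038 | .013 |

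The chance of at least one success is identical because both procedures test the smaller p-value at .025.

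**6. A smaller effect (assumed).** Let both active arms exceed the waiting list by d at T2 and T3.
- The squared interaction terms then sum to (4/9)d², so λ = 47 × (4/9)d² / 0.5 = 41.8d².
- Setting this to 21.66 gives d ≈ 0.72 as the equivalent of f = 0.16 under this pattern.
- At d = 0.5, λ = 10.4. For r from .5 to .8, the chance of confirming both rises from 46–52% to 57–62%, about 10 points.

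**The case against.** The strongest reply is that nothing here is wrong. Bonferroni is valid, it was fixed in advance, the sample size and analysis sections agree on it, and it gives simple matching simultaneous intervals. All of that stands, and it is why the point is low priority. The gain at the planned effect is small, and the 10-point gain rests on a value of d that the protocol does not give. What the reply does not remove is that Holm is never less powerful, holds the same error rate and needs no more participants.

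Three stronger readings are tempting, and the protocol does not support them.

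- A reader might infer from the word co-primary that both scales must succeed, so that splitting alpha is a mistake. Under such a rule each scale could indeed be tested at .05, with power .973 per scale. But the protocol never states a both-must-pass rule, and its threshold for each outcome points to separate claims.
- A reader might infer that the plan cannot handle a split result. The per-outcome test already implies a claim for each scale. What is absent is a sentence on wording, which an article may leave to a fuller document.
- A reader might infer that two closely correlated scales make split results common. The table shows the opposite: under Bonferroni, splits fall from 7.6% at r = .5 to 3.8% at r = .9.

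**Conclusion.** The point holds as an efficiency improvement. The rule in section 2.2.9 controls the family-wise error and matches section 2.2.4, but Holm does the same job with more power for the second scale. At f = 0.16 on both scales and 141 analysed, the gain in confirming both is 2.5 to 3.7 points for assumed between-scale correlations of .5 to .9, and 4.3 points if the scales were independent (.904 to .947). At an assumed d = 0.5 in both active arms it is about 10 points. The chance of confirming at least one scale is unchanged throughout. The sizes depend on the assumed correlation and effect pattern. Holm's error control and its advantage over Bonferroni do not.

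**What to change.** In section 2.2.9, replace the fixed threshold with wording such as: The group-by-time interaction tests for WEMWBS and MHC-SF will be tested by Holm's procedure at a family-wise α of .05, the smaller p-value at .025 and, if significant, the larger at .05. An effect is claimed separately for each scale that passes; if only one passes, the result is reported as an effect on that scale only.

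Section 2.2.4 can stay as it is, because .025 is Holm's first step, so 141 analysed and 177 recruited remain.

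The cost is a wording change made before any outcome data are compared by group, with no effect on data collection or software. The one small downside is that simultaneous intervals matching Holm are less simple than Bonferroni ones; 97.5% intervals can still be reported for each scale.

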To our knowledge, this is the first randomized controlled trial to evaluate a fully PERMA-based psychological intervention delivered via a mobile application in university students, and to directly compare a self-guided app format with a blended format that incorporates synchronous group-based telephone support. By examining not only efficacy but also adherence, satisfaction, and mechanisms of change across PERMA dimensions, this study addresses critical gaps in the digital mental health literature regarding engagement and scalability of positive psychology interventions in higher education contexts. The primary objectives of this randomized controlled trial are to: (a) assess the efficacy of a positive psychology–based psychological intervention grounded in the PERMA model in promoting psychological well-being among university students administered through a smartphone app, with (PPIA + M) and without the addition of telephone multiconference calls (PPIA), compared to a waiting list control group (WLCG); and (b) examine the mediators and moderators of change in psychological well-being. The central hypotheses are that participants in both the PPIA and PPIA+M groups will demonstrate significantly greater improvements in psychological well-being compared to the WLCG at post-treatment and 6-month follow-up, with the PPIA+M group showing more pronounced improvements due to the added telephone support; additionally, it is expected that the change in positive emotion, engagement, relationships, meaning, and accomplishment will mediate the effects of both interventions; and that sociodemographic, academic, and clinical variables, as well as satisfaction with the intervention, will moderate treatment effects. Mediation and moderation analyses are planned as exploratory and hypothesis-generating, aimed at informing future optimization of the intervention.

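### Plain Bonferroni on the three arm contrasts is valid but needlessly conservative: Shaffer's step-down rule gives the same strong family-wise control at each visit and is never less powerful

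*Protocol article*

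**What the plan says.** Section 2.2.9 (Statistical analyses) makes the group-by-time interaction the confirmatory test: "a Bonferroni-adjusted significance threshold of α = .025 will be applied to the primary confirmatory group-by-time interaction test for each outcome". It then plans three contrasts, labelled post hoc, from estimated marginal means at T2 and at T3: PPIA against the waiting list, PPIA+M against the waiting list, and PPIA+M against PPIA. On multiplicity among them it says only: "Pairwise contrasts will be adjusted using the Bonferroni correction". It gives neither the number of contrasts in a family nor the α that is divided, and it does not make the contrasts conditional on a significant interaction.

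The Introduction states the central hypotheses as arm contrasts: both active arms better than the waiting list at both time points, "with the PPIA+M group showing more pronounced improvements due to the added telephone support".

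Section 2.2.4 (Sample size calculation) powers only the omnibus interaction. It gives no power for any contrast, but describes its effect size as "approximately comparable to a standardized effect of *d/g* ≈ 0.32 under a simple two-group contrast approximation".

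**The concern.** The interaction test can show that the arms change differently over time, but not which arms differ. Among the planned analyses only the pairwise contrasts answer the stated hypotheses, so their power matters despite the post hoc label.

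Plain Bonferroni holds every contrast at one third of the family α, whatever the other contrasts show. With three arms this is stricter than it need be. Once one pair of arms is shown to differ, at most one true equality can remain among the other two, so there is only one possible false rejection left to guard against and no reason to divide α again. The ordering the trial predicts (PPIA+M above PPIA above waiting list) is where this costs most: once PPIA+M against the waiting list is established, the two smaller steps must still pass α/3 when α would suffice.

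**Working it through.** **Inputs.** From section 2.2.4: f = 0.16, d ≈ 0.32, "statistical power = .95, correlation among repeated measures = .50, and nonsphericity correction *ϵ* = 1", 141 analysable (47 per arm), 177 recruited (59 per arm). From 2.2.9: α = .025 for each outcome's interaction test, three contrasts at each of two visits. Assumed, because the protocol does not say: a family of three per outcome and visit; family α of .025 or .05; SD 1 at the visit with no precision gain from the repeated measures; all effect patterns other than d = 0.32.

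**Step 1: the plan's own figure.** λ = f²·N·m/(1−ρ) = 0.16² × 141 × 3 / 0.5 = 21.66, with df (3−1)(3−1) = 4 and (141−3)(3−1) = 276. At α = .025 the power is 0.951, against the stated .9509. Recruitment: 141/0.8 = 176.25, which becomes 59 per arm, or 177. Both reproduce. This is the power of the omnibus test only.

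**Step 2: one contrast at d = 0.32.** Noncentrality is d·√(n/2): 1.551 at n = 47 and 1.738 at n = 59, with df = 3n − 3 = 138 and 174.

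| Family α | n per arm | Unadjusted | Bonferroni (α/3) |
|---|---|---|---|
| .025 | 47 | 24.1% | 13.4% |
| .025 | 59 | 30.3% | 17.9% |
| .05 | 47 | 33.8% | 19.5% |
| .05 | 59 | 40.9% | 25.1% |

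The difference, 10.6 to 15.7 points, is the full cost of the correction. Only part of it can be recovered without losing error control.

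**Step 3: why the step-down rule is valid.** The rule tests the smallest p at α/3 and, if it is rejected, the other two at α. Three arms allow only three situations.
- All three equalities true: an error needs the smallest p below α/3, which has probability at most α.
- Exactly one true: only that one can be falsely rejected, and it is never tested above α.
- None true: no false rejection is possible.

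So family-wise error is at most α in every case. Every contrast that Bonferroni rejects has p below α/3, so Shaffer's rule rejects it too.

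**Step 4: size of the gain.** Simulation with 400,000 runs per scenario, pooled t tests, one visit. Entries are Bonferroni → Shaffer power.

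| Scenario (WLCG / PPIA / PPIA+M) | α .025, n 47 | α .025, n 59 | α .05, n 47 | α .05, n 59 |
|---|---|---|---|---|
| 0/0.32/0.32, each active arm vs WLCG | 13.4 → 15.8% | 18.0 → 21.3% | 19.5 → 23.4% | 25.2 → 30.0% |
| 0/0.32/0.64, each smaller step | 13.5 → 22.5% | 18 → 29% | 19.5 → 32% | 25 → 40% |
| 0/0.32/0.64, PPIA+M vs WLCG | 66.5 → 67.8% | 79.0 → 79.9% | 75.1 → 76.6% | 85.5 → 86.5% |
| 0/0.50/0.50, both active arms beat WLCG | 24.4 → 37.2% | 35.4 → 49.8% | 33.7 → 49.0% | 46.0 → 61.9% |

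The last row is joint power. Per contrast, the gain in that scenario is about 6 to 8 points.

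**Step 5: error rates per visit.**

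| Situation | α .025 | α .05 |
|---|---|---|
| Global null, no correction | 6.4% | 12.2% |
| Global null, Bonferroni or Shaffer (same first step) | 2.3% | 4.4% |
| One true equality, Bonferroni | 0.8% | 1.7% |
| One true equality, Shaffer (maximum, up to simulation error) | 2.5% | 5.0% |

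The extra power comes from using the part of the allotted level that Bonferroni leaves unspent under partial nulls.

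**The case against.** The strongest reply is that nothing here is wrong. Bonferroni controls the family-wise error under any dependence and is standard, and no other passage contradicts it. That stands.

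Second, a reader might infer that the correction buys no error protection, or that it treats the contrasts as independent. Neither is so. As the plan is written, Bonferroni is the only control on these contrasts. The interaction test does not replace it: it is not stated as a condition, and it spans both visits. With an assumed effect of d = 0.8 at T2 only, unadjusted contrasts entered through the interaction test would give T3 family-wise error of about 6.0% (α .025) or 12.2% (α .05).

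Third, a reader might infer a flat gain of 5 to 15 points for every contrast. The table does not support that. At the protocol's own d of 0.32 in both active arms the gain stays below 5 points. Gains of 12 to 15 points need the graded pattern at family α .05; at α .025 they are about 9 to 11. The Introduction predicts the ordering, but the sizes 0.64 and 0.50 are assumptions.

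Fourth, decisions that agree with the reported intervals are a legitimate reason to prefer Bonferroni. A contrast gained by stepping down has p between α/3 and α, so its Bonferroni interval always includes zero. This stands as a small real cost.

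Finally, the change does not cure low contrast power: at d = 0.32 it is still at most about 40% afterwards. That is true, but no reason to decline a gain that needs no participants.

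**Conclusion.** The point holds as an efficiency improvement. Plain Bonferroni is valid but stricter than three arms require, and Shaffer's rule is never less powerful at the same guaranteed per-visit level. The gain per contrast is about 2 to 5 points if both active arms have d 0.32; in the graded pattern about 9 to 15 for the two smaller steps and 1 to 1.5 for the largest. Joint power for both active arms at d 0.50 rises by about 13 to 16 points.

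These sizes rest on a family of three per outcome and visit, base α of .025 or .05, and cross-sectional contrasts with SD 1. Precision gained from the mixed model would change the absolute powers, but Shaffer's rule would still be never less powerful. The documents do not support reading this as a mistake in the plan, or as grounds for leaving the contrasts unadjusted.

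**What to change.** In section 2.2.9, replace the Bonferroni sentence with:

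> Within each outcome and visit the three pairwise p-values are tested by Shaffer's step-down procedure: the smallest at α/3 and, if it is rejected, the other two at α, where α is the level allotted to that outcome and visit.

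State that α as a number. The rule as worded controls one outcome and visit. It would not control a family of six spanning T2 and T3, so if both visits are to form one family, divide the level between them first and apply the rule within each.

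Keep the estimated marginal means and effect sizes. Because step-down decisions have no exactly matching simultaneous intervals, report unadjusted intervals labelled as such, or Bonferroni intervals with a note that a contrast rejected only at the second step will have one that includes zero.

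The cost is one sentence, with no new data and no extra participants. It should be settled before the outcome data are seen by arm.

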##### Clinical significance

2.2.9.1

As a complementary analysis, reliable change will be examined using the Jacobson and Truax approach (64). The Reliable Change Index will be calculated as RCI = (post-intervention score - baseline score)/SEdiff. Participants with RCI values greater than 1.96 will be classified as showing positive reliable change, values below -1.96 as showing negative reliable change, and values between -1.96 and 1.96 as showing no reliable change. If appropriate normative reference values are available for the WEMWBS and MHC-SF in comparable student populations, clinical significance cutoffs will also be calculated; otherwise, interpretation will focus on reliable change rather than clinical recovery.

##### Moderation and mediation analyses

2.2.9.2

Moderation and mediation analyses will be conducted as exploratory and hypothesis-generating analyses for the PPIA, PPIA+M, and WLCG groups. These analyses are not part of the primary confirmatory testing framework and will not be interpreted as demonstrating causal mechanisms.

Moderation analyses will be conducted using regression models including treatment condition, the candidate moderator, and the treatment-by-moderator interaction term. Continuous variables will be mean-centered to improve interpretation, following the recommendations of Kraemer and Blasey (65). Potential moderators will include baseline sociodemographic, academic, and clinical variables, adherence, and satisfaction with the intervention. Evidence of moderation will be considered present when the treatment-by-moderator interaction term is statistically significant, indicating that the effect of the intervention on well-being outcomes varies according to the level of the moderator.

Mediation analyses will examine whether changes in PERMA dimensions —positive emotion, engagement, relationships, meaning, and accomplishment— are associated with changes in emotional well-being and psychological, emotional, and social well-being. Changes in WEMWBS and MHC-SF scores between baseline and post-intervention will be used as dependent variables, treatment condition as the independent variable, and changes in PERMA dimensions between baseline and post-intervention as potential mediators. Indirect effects will be estimated using bias-corrected bootstrap confidence intervals with 5,000 resamples. Because mediator and outcome changes are assessed over overlapping time intervals, these analyses will be considered exploratory and will not be interpreted as demonstrating causal mechanisms.

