#### Eligibility criteria

2.2.2

Inclusion criteria include: (a) being an actively enrolled university student at the University of Santiago de Compostela (USC); and (b) having access to a smartphone with an internet connection. Exclusion criteria include: (a) having a current diagnosis of severe psychiatric disorder, including major depressive disorder with psychotic features, bipolar disorder, schizophrenia, severe cognitive impairment, dissociative disorders, active substance dependence, or active suicidal behaviors; (b) having started psychological or psychopharmacological treatment within the two months prior to the study or participating in another mental health-related study; (c) having insufficient proficiency in Spanish, or presenting sensory, cognitive, or physical impairments that would prevent engagement with the intervention; or (d) planning to move out of Galicia within the next 12 months.

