##### WLCG – Waitlist Control Group

2.2.6.3

Participants assigned to the Waitlist Control Group (WLCG) will not receive any intervention during the five-week study period but will complete all study assessments at the same time points as the experimental groups. After completing the final follow-up evaluation, participants in the WLCG will be granted access to the full PPIA mobile intervention program.

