##### Sociodemographic, academic, and clinical characteristics

2.2.7.1

To collect information on sociodemographic, academic, and clinical variables relevant to participant eligibility, a structured interviewer-administered questionnaire will be used at baseline. It will include information on sex assigned at birth, gender identity, age, marital status, living arrangements, rural/urban setting, employment status, and self-reported socioeconomic level (e.g., monthly household income and access to financial resources). Academic variables will include the current academic program and year of enrollment. Clinical data will include having initiated psychological or psychopharmacological treatment within the two months prior to the study, and currently participating in another mental health–related research study.

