###### Satisfaction with the intervention

2.2.7.4.6

Satisfaction with the intervention will be assessed at post-intervention (T2) using the Client Satisfaction Questionnaire–8 (CSQ-8 (60); Vázquez et al. (61) for the Castilian Spanish version). The CSQ-8 is an 8-item self-administered instrument rated on a 4-point Likert scale, ranging from 1 to 4, with total scores ranging from 8 to 32, where higher scores indicate greater satisfaction. The original version has demonstrated excellent internal consistency (α >.90), while the Spanish validation confirmed high internal consistency (α = .83) and strong construct validity in clinical and research contexts.

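### Adherence and satisfaction arise after randomization and have no waiting-list value, so they cannot serve as moderators in the three-arm model; the two named clinical moderators are exclusion criteria

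*Protocol article*

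**What the plan says.** Section 2.2.9.2 fixes four things about the moderation analysis.

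- **Arms.** Moderation and mediation are exploratory and "hypothesis-generating analyses for the PPIA, PPIA+M, and WLCG groups".
- **Model.** "Moderation analyses will be conducted using regression models including treatment condition, the candidate moderator, and the treatment-by-moderator interaction term".
- **Candidates.** "Potential moderators will include baseline sociodemographic, academic, and clinical variables, adherence, and satisfaction with the intervention".
- **Decision rule.** "Evidence of moderation will be considered present when the treatment-by-moderator interaction term is statistically significant". The same sentence then reads such a term as the effect on well-being differing by moderator level.

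The Introduction hypothesizes that sociodemographic, academic and clinical variables, and satisfaction, will moderate the treatment effect.

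Other sections define the variables.

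- **Adherence (2.2.7.5)** counts app modules and between-session tasks. In PPIA+M it also counts attendance at the weekly calls.
- **Satisfaction (2.2.7.4.6)** is the CSQ-8, completed at T2.
- **Waiting list (2.2.6.3)** participants "will not receive any intervention during the five-week study period" and get the app only after their final follow-up.
- **Clinical data (2.2.7.1):** "Clinical data will include having initiated psychological or psychopharmacological treatment within the two months prior to the study", plus current participation in another mental health study. Section 2.2.9 lists the same two items and no others.
- **Exclusion criterion (b) (2.2.2):** "having started psychological or psychopharmacological treatment within the two months prior to the study or participating in another mental health-related study".

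**The concern.** A moderator of a randomized treatment effect has to be defined in every arm being compared, and it should not itself be affected by allocation. Adherence and satisfaction fail on both counts when the waiting list is one of the arms. A variable that eligibility holds constant cannot moderate anything.

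Part of the moderation hypothesis therefore cannot be tested as written. What can still be fitted invites a wrong reading. Students who would have improved anyway may also complete more modules and report more satisfaction, and the stated rule would treat a significant interaction as a finding about whom the intervention helps. The Introduction says these analyses are meant to inform later optimization of the intervention, so such a finding could be acted on.

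**Working it through.** **Plan's own figure.** The protocol states no figure for the moderation analysis. The sample-size section (2.2.4) supplies the arm size: 141 / (1 − 0.20) = 176.25, raised to 177 = 3 × 59.

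**Model.** Take the waiting list as reference, D1 for PPIA, D2 for PPIA+M, and Mc for the mean-centred moderator:

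Y = b0 + b1·D1 + b2·D2 + b3·Mc + b4·D1·Mc + b5·D2·Mc

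The moderator slope is b3 in the waiting list, b3 + b4 in PPIA and b3 + b5 in PPIA+M. The interactions b4 and b5 are differences from the waiting-list slope, so they exist only if the moderator has a value and some spread in that arm.

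**Adherence, waiting list coded 0.** There Mc equals −m for everyone, where m is the overall mean. Hence Mc = −m·(1 − D1 − D2) + D1·Mc + D2·Mc exactly. One of the six columns is redundant, and b3, b4 and b5 cannot all be estimated. Only b5 − b4, the difference between the two active arms, is identified.

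**Satisfaction, absent in the waiting list.** The rows left are 2 × 59 = 118 of 177. The model reduces to four columns (intercept, arm, satisfaction, arm-by-satisfaction) and holds no contrast with the waiting list.

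**Named clinical items, all coded no.** Mc = 0 for everyone, so the last three columns are zero.

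Ranks computed with 59 per arm:

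| Moderator | Rows | Columns | Rank | Interaction with waiting list |
|---|---|---|---|---|
| Baseline variable that varies (age) | 177 | 6 | 6 | estimable |
| Adherence, waiting list = 0 | 177 | 6 | 5 | not estimable |
| Satisfaction, active arms only | 118 | 4 | 4 | none in model |
| Named clinical item, constant | 177 | 6 | 3 | not estimable |

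**What remains between PPIA and PPIA+M.** The interaction can be fitted, but three passages limit its meaning.

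1. Both variables are recorded after allocation (2.2.7.4.6, 2.2.7.5), so participants with equal scores in the two arms are no longer groups that randomization made comparable.
2. The Discussion expects higher adherence in PPIA+M, so adherence is partly a result of the treatment being compared.
3. Adherence in PPIA+M includes call attendance, which has no counterpart in PPIA, so the same score does not mean the same thing.

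**Clinical items side by side.** Section 2.2.7.1 names recent start of psychological or drug treatment and participation in another mental health study. Criterion (b) excludes on exactly these two.

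**Count.** Sections 2.2.7.1 and 2.2.9 name 8 sociodemographic, 2 academic and 2 clinical variables. Adding adherence and satisfaction gives 8 + 2 + 2 + 1 + 1 = 14. Of these, 2 + 1 + 1 = 4 cannot be tested against the waiting list, and 10 remain.

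**The case against.** The strongest defence is the exploratory label. The Introduction and 2.2.9.2 both call these analyses hypothesis-generating, and 2.2.9.2 places them outside confirmatory testing and rules out claims about causal mechanisms. That stands and limits the severity. It does not make a redundant term estimable, and 2.2.9.2 still reads a significant interaction as the effect differing by moderator level.

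It can also be said that the waiting list completes all assessments (2.2.6.3), so a CSQ-8 form might formally be filled in. It would not rate an intervention that the respondent had received.

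Four stronger readings are tempting, and the document does not support them.

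- **Clinical variables in general are untestable.** Section 2.2.7.1 is worded as an inclusive list, only severe disorders are excluded, and the SCID-5-CV covers a wide range of conditions, so diagnosis could vary among those randomized. Against this, 2.2.9 repeats only the two items, and Table 2 lists mental disorders separately. The point holds for the two named items only.
- **Waiting-list satisfaction would be imputed.** Section 2.2.9 plans multiple imputation for missing data but does not say that it extends to the CSQ-8 in that arm.
- **Both variables are predicted to differ by arm.** The Discussion predicts this for adherence; no passage predicts higher satisfaction in PPIA+M.
- **A definite rate of false moderators follows.** The protocol gives no significance level for moderation, no number of tests and no dependence structure, so no rate can be derived. How an exploratory analysis handles multiplicity may be left to the analysis plan.

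**Conclusion.** The point holds for adherence and satisfaction. As specified, neither can be tested as a moderator of the effect against the waiting list. The comparison between the active arms can be computed, but it would not show effect modification by a participant characteristic. This follows from the definitions and timing in the protocol and needs no outside figure.

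The clinical-variable point is secondary. It covers the two named items and assumes that criterion (b) is applied to everyone randomized.

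The size is 4 of 14 named candidates; the other 10 are baseline variables and fit the model as long as they vary. A reader might infer that the trial's main conclusions are at risk. They are not, because the group-by-time tests on the WEMWBS and MHC-SF, their significance level and the sample size do not depend on this analysis. The text should be corrected, but no confirmatory result hinges on it.

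**What to change.** Change 2.2.9.2, and align the moderation hypothesis in the Introduction.

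1. Restrict moderators to baseline variables that can vary among randomized participants. The three-arm model is then of full rank (6 of 6 in the check with age).
2. Replace the two constant clinical items with baseline data already collected, such as baseline WEMWBS or MHC-SF score, or SCID-5-CV diagnoses that do not lead to exclusion.
3. Take adherence and satisfaction out of the moderator list and the hypothesis. Analyse them within PPIA and PPIA+M only, as non-causal associations with outcome, and do not call this moderation.
4. For that analysis define adherence the same way in both arms, for example by modules and tasks completed, and report call attendance separately for PPIA+M.

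The cost is rewording two passages. No new data, assessments or participants are needed, and the confirmatory analysis stays as it is.
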